# METHODS

## Study parameters/endpoints

### Main study parameter/endpoint

Percent total weight loss (%TWL) at 5 years.

Assumptions : Control group : TWL of 35% (SD 12%)

Experimental group : TWL of 40% (SD 12 or 9%)

(Absolute difference TWL 5% with possible smaller SD)

Definition : TWL = ([initial weight – attained weight]/ initial weight) * 100

### Secondary study parameters/endpoints

1) Percent of total weight loss (%TWL) at 1,2,3,and 4 years.

2) Percent excess weight loss (%EWL) at 1,2,3, 4 and 5 years.

Definition: %EWL (Initial Weight – Postop Weight) / (Initial Weight – Ideal Weight)

(ideal weight is defined by the weight corresponding to a BMI of 25 kg/m2 )

3) Percent excess BMI loss (%EBMIL) at 1,2,3, 4 and 5 years.

Definition: %EBMIL (ΔBMI / (Initial BMI – 25)) * 100]

4) Proportion of patients with 22 ≤ BMI ≤ 30 Kg/m^2^ at 1,2,3, 4 and 5 years

5) Mean number of daily bowel movements in the last two weeks at 6 months, 1,2,3, 4 and 5 years.

6) Mean number of days with daily bowel movements > 3 in the last two weeks at 6 months, 1,2,3, 4 and 5 years.

6) Quality of life measured by the RAND-36 questionnaire at 6 months, 1,2,3, 4 and 5 years, absolute and compared to before surgery.

7) percentage of patients experiencing moderate to severe dumping symptoms defined by the Dumping Severity Score (DSS) at 6 months, 1,2,3, 4 and 5 years, absolute and compared to before surgery.

Moderate to severe is defined as 3 or more dumping symptoms with a severity score of 2 or 3 on a 4-point Likert scale. Symptoms are divided in two categories, e.g. early and late,

as described by Emous et.al. (7)

8) percentage of patients who have neither deficiencies of iron, nor vit. D, nor vit B12 without extra suppletion, at 6 months, 1,2,3, 4 and 5 years . Deficiencies are based on the local normal laboratory values.

9) Proportion of patients who have a deficiency at 6 months, 1,2,3, 4 and 5 years, or received extra suppletion for:

- iron (ferritin)

- vitamin B_12_

- vitamin D_3_

- Vitamin B_1_

- Vitamin B_6_

- Folic acid

- Vitamin A

- Vitamin D

- Calcium

- Phosphate

- Albumin

- Zinc

- Copper at 1,3 or 5 years

- Selenium at 1,3 or 5 years

10)Proportion of patients at 1,2,3, 4 and 5 years without diabetes, both with remission and without de novo, defined as an HbA1c less than 48 mmol/mol without diabetes medication in the last 6 months.

11)Proportion of patients at one year and two years with improvement of diabetes, defined as a reduction of HbA1c of 10mmol/mol or more but not reaching remission criteria and/or less anti-diabetic medication.

12)Proportion of patients at 1,2,3, 4 and 5 years with remission of hypertension, defined as a blood pressure of 140/90 mmHg or less without antihypertensive medication.

13)Proportion of patients at 1,2,3, 4 and 5 years with improvement of hypertension, defined as a lower blood pressure and/or less antihypertensive medication (not reaching the criterion of remission).

14)Proportion of patients at 1,2,3, 4 and 5 years with resolution of sleep apnea, defined by cessation of CPAP or other devices use, documented by their own pulmonologist

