**Nature and extent of the burden and risks associated with participation, benefit and group relatedness:**

Measuring TSBL will take 10 minutes of extra time during the surgery and increases slightly the risk of damaging the intestine. Bariatric surgeons are experienced in measuring small bowel. Patients have 4 extra visits in 5 years and during routine blood testing an extra bloodsample of 20 ml will be drawn for research purposes. They have to fill in 2 questionnaires at their visits. Benefit is a free providing of a daily multivitamin capsule during the study and possibly a better outcome after surgery in terms of weight loss and side effects.

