**Secondary Objective(s):**

1) To compare the percent of total weight loss (%TWL) between the groups at 1,2,3 and 4 years.

2) To compare the percent excess weight loss (%EWL) between the groups at 1,2,3, 4 and 5 years.

Definition: %EWL (Initial Weight – Postop Weight) / (Initial Weight – Ideal Weight)

(ideal weight is defined by the weight corresponding to a BMI of 25 kg/m2 )

3) To compare the percent excess BMI loss (%EBMIL) between the groups at 1,2, 3, 4 and 5 years.

Definition: %EBMIL (ΔBMI / (Initial BMI – 25)) * 100)

4) To compare the proportion of patients with 22 ≤ BMI ≤ 30 between the groups at 1,2 3, 4 and 5 years.

5) To compare the mean number of daily bowel movements and number of days with daily bowel movements > 3 in the last two weeks, between the groups at 6 months, 1,2, 3, 4, and 5 years.

6) To compare the Quality of life measured by the RAND-36 questionnaire between the groups at 6 months, 1,2, 3, 4 and 5 years, absolute and compared to before surgery

7) To compare the percentage of patients experiencing moderate to severe dumping symptoms defined by the Dumping Severity Score (DSS) (see Emous et al.) at 6 months, year 1, 2, 3, 4 and 5 between the groups, absolute and compared to before surgery.

8) To compare the proportion of patients in the two groups who have neither deficiencies of iron, nor vit. D, nor vit B12 without extra suppletion, at 6 months, 1, 2, 3, 4 and 5 years. Deficiencies are defined by the lower border of the local normal laboratory values.

9) To compare the proportion of patients in the two groups who have a deficiency at 6 months, 1, 2, 3, 4 and 5 years, or received extra suppletion for :

- Vitamin B1

- Vitamin B6

- Folic acid

- Vitamin A

- Vitamin D

- Calcium

- Phosphate

- Albumin

- Zinc

- Copper (visit 1,3,5 years)

- Selenium (visit 1,3,5 years)

Deficiencies are defined by the lower border of the local normal laboratory values.

10)To compare the proportion of patients between the groups at 1, 2, 3, 4 and 5 years without diabetes, both those with remission of diabetes and those without de novo diabetes, defined as an HbA1c less than 48 mmol/mol without diabetes medication in the last 6 months. ^#^

11) To compare the proportion of patients between the groups at 1, 2, 3,4 and 5 years with improvement of diabetes, defined as a reduction of HbA1c with at least 10 mmol/mol, but not reaching remission criteria and/or less anti-diabetic medication ^#^.

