## Study procedures

A standard operation protocol for OLGB will be used in all patients. The pouch will be made with the help of a linear stapler. At first, the stomach will be transected horizontally at the junction of the corpus and antrum at the level of crow’s foot. A small pouch is made with help of a calibration sonde of 34 French, the pouch is finished near the angle of His. Then the total limb length is measured. With a succesfull TSBL measurement the OR nurse will open the envelop and the allocated procedure will be communicated to the surgeon. Based on the randomization outcome biliopancreatic limb length is measured. In case the measurement of the total limb length does not succeed, standard limb length of 150 cm is performed. An antecolic, retrogastric anastomosis is performed by liniar stapling and the remaining defect is closed by V-loc. An anti-reflux stitch is performed. Integrity of the anastomoses is checked by methylene-blue-test and in case of leakage, extra sutures will be applied. The mesenterial defect of Peterson will be closed as far as possible by endo hernia stapling or unresolvable V-loc.

The extra measurements of limb length will take less than ten minutes of time. In patients allocated to standard treatment the surgeon will construct a BP-limb of 150 cm. In patients allocated to the adjustment length, the length of the BP-limb will depend on the total small bowel length : < 500 cm : 150 BP; 500-700 cm : 180 BP and > 700 cm : 210 BP.

On leave of the hospital the patients will be provided with Fitforme WSL Primo multivitamin capsules for the following period and will be instructed to use one capsule once daily.

Follow-up will take place in accordance with usual care, i.e. after 1,6,12 and 24 months and yearly up till 5 years. Extra visits will be at 18,30,42 and 54 months for compliance check and distribution of FFM multivitamins.

Weight measurements and blood samples will be taken in accordance with the standard protocol of follow-up after bariatric surgery in our institute added with 20 ml for selenium and copper measurements and future lab tests at 1,3 and 5 years.

Data from 6,12 and 24 months and every year thereafter up to five years after surgery will be anonymously collected in a database.

At each visit standard care includes :

- inquiry after well being and complaints, side effects, adverse events
- documenting current medication use, both regular and over-the-counter, and when applicable CPAP use

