- inquiring after co-morbidities
- measurement of body weight, blood pressure and pulse
- drawing of blood samples for routine post operative care including :

CRP, hemoglobin, WBC, thrombocytes, sodium, potassium, creatinin, BUN, ASAT, ALAT, alkaline phosphatase, yGT, HbA1c, glucose, calcium, magnesium, phosphate, albumin, vit B_1_, vit B_6_, vit B_12_, folic acid, ferritin, vit A, vit D, Zinc

- Scheduling a new appointment

If the patient forgot to bring along a recent overview of current medication from their own pharmacy , the actual medication use will be requested from the local pharmacy.

Extra effort for the patient in the study includes :

- Bringing along a written overview of current medication from the local pharmacy to the appointment.
- Bringing back all used and non-used blisters and boxes for counting of compliance of the use of the FitForMe WLS primo pills
- filling in the DSS questionnaire
- filling in the RAND 36 questionnaire
- drawing of 20 ml of extra blood during the venepuncture for selenium, copper and storage for later investigations at 1,3 and 5 years
- Visits at 18, 30,42, and 54 months for counting left over pills and distributing new ones for the forthcoming 6 months

All patients will be treated with 800 IU vitamin D and 500 mg Calcium in a combination pill as part of standard care.

In case of deficiencies of vitamins or micronutrients they will be substituted according to standard care.

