## Recruitment and consent

Patients will be asked to participate during their visit to their surgeon before the surgery after they have decided for an OLGB. After short verbal explanation of the study, they will be provided with the written patient information and consent form. After 1-2 weeks they will be approached by telephone. When they have decided to participate they will have a meeting with the investigator on admission the day before surgery. Any questions still not answered will be addressed and the informed consent form will be signed by the patient and the investigator twice (one copy for the patient). After this procedure the patient will be asked to swallow 1 Fitforme WLS primo capsule in order to see whether they arte able to swallow the capsule. If not, the patient will drop out of the study and will be replaced

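### RAND-36 and Dumping Severity Score are to be compared with before surgery, but the protocol schedules no pre-operative administration of either questionnaire

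*Protocol*

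**What the plan says.** Two secondary endpoints in protocol section 7.1.2 refer back to the pre-operative state. The RAND-36 item reads "Quality of life measured by the RAND-36 questionnaire at 6 months, 1,2,3, 4 and 5 years, absolute and compared to before surgery". The dumping item is the percentage of patients with moderate to severe symptoms "defined by the Dumping Severity Score (DSS) at 6 months, 1,2,3, 4 and 5 years, absolute and compared to before surgery". Secondary objectives 6 and 7 in section 2 ask for the same between-group comparisons, again "absolute and compared to before surgery".

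On collection, the protocol says the following.

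- Section 7.3, visits: "Follow-up will take place in accordance with usual care, i.e. after 1,6,12 and 24 months and yearly up till 5 years", with extra visits at 18, 30, 42 and 54 months.
- Section 7.3, database: "Data from 6,12 and 24 months and every year thereafter up to five years after surgery will be anonymously collected in a database".
- Section 7.3, patient effort: "filling in the RAND 36 questionnaire" and the DSS appear in the list of extra effort for the study, not in the list of standard care. No time point is attached to either.
- Summary, burden paragraph: "They have to fill in 2 questionnaires at their visits".
- Section 10.2: on admission the day before surgery the investigator answers remaining questions and consent is signed. "After this procedure the patient will be asked to swallow 1 Fitforme WLS primo capsule". No questionnaire is mentioned.
- Section 9, baseline characteristics: baseline values of the study endpoints will be tabulated where applicable.

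**The concern.** The endpoint definitions require a before-surgery score on two instruments, and the operational sections never say when that score is obtained. Sites work from the procedures section. If a questionnaire is not listed there for the pre-operative contact, it may be missed, or taken at different moments by different staff.

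The loss would be permanent, since a quality-of-life or dumping score from before the operation cannot be obtained afterwards. Section 9 also rules out estimating or replacing missing values. A patient without a pre-operative score would therefore drop out of the change comparison at every follow-up time. A statistical analysis plan cannot repair this, because it cannot create an assessment that was never made.

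**Working it through.** **Step 1: what is needed and what is provided.** The stated plan reports no figure to reproduce here, so the check sets the sections side by side.

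| Time point for RAND-36 and DSS | Required by objectives and endpoints | Covered by visit schedule or data-collection sentence |
|---|---|---|
| Before surgery | Yes | No statement |
| 6 months | Yes | Yes |
| 1, 2, 3, 4, 5 years | Yes | Yes |

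Six post-operative time points are covered and the one pre-operative time point is not. Each change comparison uses that single value, so 2 instruments × 6 times = 12 change comparisons depend on it.

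**Step 2: could the value come from elsewhere?** The data-collection sentence also leaves out pre-operative weight, HbA1c and blood pressure, which other endpoints need. For those there is a visible source. Section 4 sets eligibility by BMI, section 7.3 lists weight, blood pressure and HbA1c under standard care, and section 9 names weight, height and vital signs in the baseline description. RAND-36 and DSS have no such source. Section 7.3 places them outside standard care, so a chart value cannot be presumed.

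**Step 3: could it come from the pre-operative contacts?** Section 10.2 describes the surgeon visit where the study is introduced, a telephone call 1-2 weeks later, and the admission meeting. The first two precede signed consent. The third lists questions, consent and the capsule test only.

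**Step 4: what a RAND-36 baseline would add.** Section 9.2 applies the primary approach to quantitative secondary endpoints: a two-sample t-test, or a Mann-Whitney test if the data are skewed. Neither uses the baseline. With the before-surgery score as covariate, and correlation ρ between baseline and follow-up, the residual variance is multiplied by 1 − ρ². The number per arm that would give the same precision unadjusted is n / (1 − ρ²). Take n = 92 per arm from section 4.4, before the drop-out allowance. The protocol gives no ρ, so 0.4 to 0.6 is an assumed range.

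| ρ (assumed) | 1 − ρ² | Variance reduction | 92 / (1 − ρ²) |
|---|---|---|---|
| 0.4 | 0.84 | 16% | 109.5, about 110 |
| 0.5 | 0.75 | 25% | 122.7, about 123 |
| 0.6 | 0.64 | 36% | 143.8, about 144 |

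**The case against.** The strongest reply is that the protocol does call for the measurement. Two objectives and two endpoints are defined against the pre-operative state, and section 9 plans to tabulate baseline values of endpoints. On that view only the day and a database line are missing. This is fair as to intent, and it stands: the sponsor most likely meant to take a baseline. It does not close the gap, because the statement in section 9 concerns reporting and no procedure produces the two values.

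A reader might go further and infer that the questionnaires start only after surgery, so that the change endpoints cannot be computed. The documents do not support this. No section gives a start time for either questionnaire; section 7.3 attaches no time point and the Summary speaks only of visits. Nor can the data-collection sentence be read as exhaustive. Since it omits initial weight, that reading would make the primary endpoint, percent total weight loss, incomputable as well.

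It can also be said that covariate adjustment is an optional refinement and that the correlations are assumed. Both are true. The scheduling gap stands without those figures. They show only a further benefit of taking the baseline.

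Finally, scores taken on the eve of surgery might be coloured by anticipation. The documents give no evidence on this. The allocation envelope is opened during the operation, so any such effect would precede allocation and would not be expected to differ between arms.

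**Conclusion.** The point holds as a gap between endpoint and procedure. RAND-36 and DSS are to be compared with before surgery, and baseline values are implied, but no visit, procedure or data-collection statement provides a pre-operative administration. Neither questionnaire belongs to standard care as the protocol lists it, so there is no evident fallback.

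The reach is limited to the change component of two secondary endpoints. The primary endpoint is untouched. So are the absolute between-arm comparisons of RAND-36 and DSS at all six follow-up times, which need no baseline because the arms are randomised. The matter still deserves an amendment, because the omission is cheap to correct beforehand and cannot be corrected later.

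The conclusion rests on reading the protocol alone; a case report form or site manual that already schedules the baseline would reduce it to a wording correction. The 16% to 36% variance reduction rests on the assumed correlations of 0.4 to 0.6.

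**What to change.** 1. Add to section 7.3 one RAND-36 and one DSS, completed after signed consent and before surgery and randomisation. The admission meeting in section 10.2 is a suitable moment. Completion at home beforehand would put a study procedure ahead of signed consent.
2. Add a baseline time point to the data-collection sentence in section 7.3, and mention the pre-operative administration in the Summary's burden paragraph.
3. In section 9.2, compare RAND-36 between arms at each visit with the before-surgery score as a covariate, in place of the unadjusted two-sample test.
4. If the sponsor does not intend to take a baseline, remove the comparison with before surgery from secondary objectives 6 and 7 and from the matching endpoints in section 7.1.2.

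The cost is a small amendment and a few minutes of patient time for two questionnaires already in use. Some patients will complete them and then not be randomised, for example when the small bowel cannot be measured. Giving the questionnaires after the capsule test would spare those who fail it.

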## Sample size calculation

The null hypothesis in the study is as follows : the percentage TWL at five years in both groups is not different with a mean of 35. The alternative hypothesis is that the mean of the absolute difference in TWL in the experimental group is 5% more than the standard group (40% and 35% respectively).

For the evaluation of the primary endpoint of the percent total weight loss (%TWL) at five years, a sample size of 2x 92 will achieve 80% power to detect a (absolute) difference of -5.0% between the null hypothesis ( both group means of %TWL are 35.0) and the alternative hypothesis (mean of experimental group is a %TWL of 40.0) with estimated group standard deviations of 12.0 and 12.0 and with a significance level (alpha) of 0.05 using a two-sided two-sample t-test.

In case of a reduced standard deviation in the active treatment group of 9.0, the power achieved is 88.8%.

With an expected maximum drop-out due to conversion of OAGB to RYGB of 15% the sample size is 92 plus 14 = 106 patients in each group, leading to a total of 212 participants in the study.

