## Statistical differences will not be formally evaluated. If differences are considered clinically relevant, caution will be taken when interpreting the results of the analyses between groups and the statistical methods may be modified to adjust for this difference. (By definition, differences between the randomised treatment groups at baseline are due to chance only.)

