## For qualitative parameters (categorical or ordered), frequency counts and percentages of each category will be calculated by treatment group. Percentages will be reported up to 1 decimal place.

## Primary study parameter(s)

The primary null hypothesis for this study is that there is no significant difference in the mean change in the percent of total weight loss (%TWL) at five years, between patients treated with a TSBL adjusted BP limb length (active group) versus patients treated with a standard BP limb length of 150 cm (control group).

In addition to the descriptive statistics (see the above section : Patient demographics other baseline characteristics), the two treatment strategy groups will be compared using two-sample T-test if parameter is normally distributed. Visual inspection of the distribution, as well as the Shapiro-Wilk test for normality, will used to assess normality. Unless equality of variance between groups is established, the Satterthwaite method for t-statistics and 95% confidence intervals will be used. If data is skewedly distributed, a Mann-Whitney U-test (Wilcoxon two-sample test) will be applied. For the difference in medians, the Hodges-Lehmann estimate will be used with distribution-free 95% confidence intervals.

In addition to the above mentioned analyses, the homogeneity of treatment effect over different strata of patients will be evaluated. In this, differences in treatment effect over separate strata of potentially relevant factors (e.g. gender, baseline BMI, co-morbidities, compliance, etc) will be evaluated. A multivariable model will be used to formally establish homogeneity, i.e. the absence of effect modification for the potentially relevant factors, separately.

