## Secondary study parameter(s)

All secondary endpoint parameters (quantitative and qualitative) will be presented as described in section : Patient demographics other baseline characteristics.

For the evaluation of differences between groups, the primary analysis approach will be applied for the quantitative secondairy endpoint parameters..

For the qualitative parameters a Fisher exact test or a Chi-square test will be used.

For the parameters related to the occurrence of side effects, the evaluation focusses on the “absence” of differences. For these analysis estimates of risk differences with 90% confidence intervals, based on the Farrington-Manning Method will be used (non-inferiority setting, one sided approach). Due to sample size constraints, formal hypothesis tests on non-inferiority will not be performed. Multivariable logistic (or log-binomial) regression modelling is not foreseen.

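### RAND-36 is compared between arms by unadjusted tests on both absolute and change scores, with no precedence, although the required pre-surgery score would allow one more precise, baseline-adjusted comparison

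*Protocol*

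**What the plan says.** Secondary objective 6 in section 2 makes quality of life a between-arm comparison in two forms: "To compare the Quality of life measured by the RAND-36 questionnaire between the groups at 6 months, 1,2, 3, 4 and 5 years, absolute and" then relative to the pre-surgery value. Section 7.1.2 repeats this in the endpoint list: "Quality of life measured by the RAND-36 questionnaire at 6 months, 1,2,3, 4 and 5 years, absolute and compared to before surgery". A pre-surgery RAND-36 score is therefore required.

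For the method, section 9.2 says that "the primary analysis approach will be applied for the quantitative secondairy endpoint parameters". Section 9.1 defines that approach: "the two treatment strategy groups will be compared using two-sample T-test if parameter is normally distributed". It uses the Satterthwaite form unless equal variances are established, and Mann-Whitney with a Hodges-Lehmann estimate if the data are skewed. No baseline covariate enters.

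Two other places in section 9 bear on the point. The text on baseline characteristics allows that, if a baseline difference is judged clinically relevant, "the statistical methods may be modified to adjust for this difference". The text on missing data rules out estimating or replacing missing values.

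**The concern.** With six visits and two forms, each RAND-36 scale yields 12 unadjusted between-arm results. The protocol does not say which form counts at a given visit. The absolute score ignores where each patient started. The change score subtracts the whole baseline value, which adds noise when baseline and follow-up are only weakly correlated. When the arms differ by chance before surgery, the two forms give different estimates of the same effect, and a reader or author can lean on either. The section 9.1 normality check could even send one form to a difference in means and the other to a Hodges-Lehmann shift.

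At stake are the clarity and precision of a secondary endpoint that the Summary lists among its objectives and endpoints. The primary result is not involved.

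**Working it through.** **The protocol's own figure first.** Section 4.4 states that "a sample size of 2x 92 will achieve 80% power to detect a (absolute) difference of -5.0" percentage points of %TWL, "with estimated group standard deviations of 12.0 and 12.0 and with a significance level (alpha) of 0.05 using a two-sided two-sample t-test". Exact noncentral-t power for a difference of 5 and SD 12 is 79.8% at 91 per arm and 80.3% at 92, so the stated 92 reproduces. With SD 9 in the experimental arm the result is 88.9%, against the stated 88.8%. These figures are for %TWL. The protocol gives no power, effect, SD or correlation for RAND-36.

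**How far apart the two estimates can be.** In the same patients,

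change-score difference between arms = absolute-score difference − baseline difference.

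The gap is exactly the chance baseline imbalance. With 92 per arm its standard error is √(2/92) = 0.147 baseline SDs. The probability that the two estimates differ by at least 0.1 baseline SD is P(|Z| > 0.1/0.147) = P(|Z| > 0.68), about 50%. This step needs no assumed correlation.

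**Relative precision.** Let the follow-up SD be 1, the baseline SD be k, and the correlation be ρ. Variances per patient are:

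- absolute score: 1
- change score: 1 + k² − 2kρ, which is 2(1 − ρ) when k = 1
- adjusted for baseline: 1 − ρ²

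The adjusted variance never exceeds 1. Change minus adjusted is k² − 2kρ + ρ² = (k − ρ)², which is never negative. So in large samples adjustment is at least as precise as either planned form, whatever ρ and k are. The change score is noisier than the absolute score when ρ < k/2. That threshold is 0.5 only if the SDs are equal; it is 0.4 for k = 0.8 and 0.625 for k = 1.25.

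**Power, under stated assumptions.** Assumptions: 92 per arm, two-sided alpha 0.05, k = 1, the t-test route, and an effect of 5/12 = 0.417 SD. That effect is borrowed from %TWL (section 7.1.1: "Absolute difference TWL 5% with possible smaller SD"; control SD 12). It is the size that the absolute-score test detects with about 80% power.

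| ρ | Absolute | Change | Adjusted | Gain over absolute (points) | Gain over better of the two (points) |
|---|---|---|---|---|---|
| 0.3 | 80.3% | 66.1% | 83.8% | 3.5 | 3.5 |
| 0.4 | 80.3% | 72.8% | 86.6% | 6.3 | 6.3 |
| 0.5 | 80.3% | 80.3% | 90.1% | 9.8 | 9.8 |
| 0.6 | 80.3% | 88.2% | 94.0% | 13.7 | 5.8 |
| 0.7 | 80.3% | 95.2% | 97.6% | 17.3 | 2.3 |

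At ρ = 0.5 the variance falls by 25% (1 − 0.5² = 0.75). Among the correlations shown, the gain over the better planned test is largest there.

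**Sensitivity to the assumed effect, at ρ = 0.5.** Both planned tests have equal power here. Power rises from 27.1% to 34.4% for 0.2 SD, from 52.6% to 64.7% for 0.3 SD, and from 92.1% to 97.4% for 0.5 SD. The direction is fixed, but the number of points depends on the effect.

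**The case against.** The strongest reply is that nothing planned is wrong. In a randomised trial the absolute and change comparisons are both unbiased for the same effect. RAND-36 is an unpowered secondary endpoint, and covariates are often settled in an analysis plan. The first two statements stand, so this is a matter of precision and clarity and not of bias. The third does not dispose of the point: sections 9.1 and 9.2 already fix the tests, and those tests carry no covariate.

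A second reply is that section 9 already allows adjustment when a baseline imbalance matters, which is just when the two forms disagree. The clause does address that case. But it is optional, has no threshold or model, and acts only after the imbalance has been seen. It adds a possible third analysis without saying which one governs.

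A third reply concerns skewness. The protocol sends skewed scores to Mann-Whitney, and the power figures above cover only the t-test route. That is fair, and the replacement has to provide for skewed scores.

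A reader might infer that the plan loses about 10 points of power outright. The documents do not support that. The figure needs a correlation of 0.5 and a borrowed effect size, and 0.5 is also the most favourable of the correlations shown against the better planned test. Nor does one adjusted comparison remove all room for selective reading: several scales and six visits remain.

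**Conclusion.** The point holds as a low-severity improvement. The protocol fixes two unadjusted between-arm comparisons of RAND-36 at each visit, gives neither precedence, and leaves the required pre-surgery score out of the model. That a baseline-adjusted comparison is at least as precise as both follows from the variance formulas, in large samples and without assumed values.

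The size is conditional. For correlations from 0.3 to 0.7, with equal SDs, 92 per arm and an effect of 0.417 SD, the gain is 3.5 to 17.3 points of power over the absolute score and 2.3 to 9.8 points over the better of the two planned tests. No RAND-36 figure in the protocol narrows this range. It would be wrong to infer that the planned tests are biased, or that the trial's stated 80% power for %TWL is reduced; neither follows.

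**What to change.** In section 9.2, with matching edits to secondary objective 6 and the RAND-36 item in section 7.1.2, state that for each RAND-36 scale and visit the between-arm comparison is a linear model of the follow-up score on arm and the pre-surgery score of that scale. Report the adjusted mean difference with its 95% confidence interval, using robust standard errors if scores are skewed. Show absolute and change values by arm descriptively, without separate tests.

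State how patients without a pre-surgery score are handled. One option is to leave them out of this model, which agrees with the section 9 text on missing data. The other is to keep them by imputing the baseline covariate only, written as an explicit exception to that text.

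The cost is a small change of protocol wording, since the objective, endpoint and method all stand in the protocol, and the loss of the separate unadjusted tests. No extra patients, visits or measurements are needed, because the endpoint already requires the pre-surgery score.
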